· Residential status at 4 and 12 months and number of days in own home during the first four months. This is based upon best available information from patient, family, or the local municipality (computerised information held by the local health authorities, and registered in the same way by all municipalities in Norway in the data program Gerica).

· The Barthel ADL Index [38], a ten items index of primary activities of daily living (eating, grooming, toileting etc.), adding up to a sumscore ranging from 0 to 20. The Barthel Index is sensitive to differences among persons with severe or moderate disabilities (but has a profound ceiling effect). The scoring will be based upon proxy information from the best available source (relative, nurse etc). The Barthel Index will be scored at 4 and 12 months postoperatively.

· The Nottingham Extended ADL Index (NEADL) [48], assessing instrumental ADLs like handling money and using public transportation, adding up to a sumscore of maximum 66, and having good sensitivity in the upper part of the functional range, where the Barthel Index functions poorly. Scoring is based upon proxy information 4 and 12 months postoperatively. Prior research indicate that when observation by a geriatric nurse or an occupational therapist is the reference, close relatives tend to under-estimate the patient’s functional performance, cognitively impaired patients tend to overestimate it, whereas cognitively well functioning patients tend to give fairly accurate reports [49-51]. In order to minimise variance, and since a high number of our patients will be cognitively impaired, we do the ADL scores bases on proxy information from relatives or nursing home staff in all the patients.

· Score of the Short Physical Performance Battery (SPPB), a simple test of mobility that can be scored in approximately five minutes and adds up to a sumscore of 0–16 [52]. This score is also primary endpoint in the similar RCT going on in Trondheim, Norway [53]. We have agreed with the Trondheim group to register this endpoint in exactly the same way as they do, thus facilitating pooling of results from the two trials. SPPB will be scored at 4 and 12 months.

### Background variables

The following variables will be registered for descriptive purposes and in order to assess balance between the groups with respect to prognosis:

· Demographics

· Charlson Comorbidity Index [54] and ASA score [55]

· APACHE score [56] and SAPS II [57] for physiological disruption on admittance

· IQCODE score (by close relative or staff in nursing home or home nursing) for pre-fracture cognitive decline

· CDR score (based on the combination of assessment of the patient and interview of a carer)

· Cornell scale for depression in dementia [58]

· Hand grip strength (hand dynamometry) postoperatively and after 4 and 12 months.

· Pre-fracture independence in ADL (Barthel Index and NEADL scored by close relative or nursing home staff)

· Medication

· Body Mass Index

· Type of fracture; surgical and anaesthetic procedures.

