### Data analyses and statistical power

The primary analyses will be done in a modified intention-to-treat analysis including the sample of patients completing the CERAD 10 words test and CDR at 4 months. The weighting of the components of the primary endpoint (see primary endpoint section above) will be definitely decided upon before any analyses of the treatment effect are initiated. A separate per protocol analysis will be undertaken. The primary endpoint will be analysed by stratified linear regression. If the assumption of normality turns out to be violated, additional analyses will be performed on transformed data as well as by non-parametric methods (Mann–Whitney test). Binary outcomes will be analysed by chi square tests and logistic regression models. The material will be checked for any inequality in the distribution of important prognostic variables between the two arms, and if such are present, they will be adjusted for by including these in appropriate regression models.

Sensitivity analyses will be performed by imputing missing values in different conservative ways, e.g. by imputing the worst observed score of the treatment group and also by random sampling from the observed scores in the treatment group.

The main analyses of 12 months data will be carried out including patients with responses registered at that time point. Additional sensitivity analyses will be performed in the sample of all randomised patients using different methods of imputation as described above as well as by carrying the four month observation forward.

If an interaction test is statistically significant at the 0.10 level, we will analyse the effect upon the endpoints separately in the following subgroups: patients admitted from nursing homes or not, and patients with and without pre-fracture dementia.

We also register the time window from admittance to start of surgery, as any group difference here may also impact severely on the outcome [7].

No data are available allowing us to carry out precise power estimates based on our primary endpoint. Based upon previous experiences with CDR, however [61] ([name], unpublished data), we judge 300 patients to be sufficient to detect clinically meaningful differences. As 20% of hip fracture patients can be expected to die before the 4 months follow up [6], we aim for 370 patients to be randomised.

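### As stated, the 4- and 12-month Barthel and NEADL comparisons would usually leave out the same scale's pre-fracture score, which costs precision

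*Protocol article*

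**What the plan says.** Under Secondary objectives, the protocol article names the effect on activities of daily living at 4 and 12 months. Under Secondary endpoints, it measures this with two scales. For Barthel: "The Barthel Index will be scored at 4 and 12 months postoperatively". For NEADL: "Scoring is based upon proxy information 4 and 12 months postoperatively".

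The Background variables section lists the pre-fracture values of both scales: "Pre-fracture independence in ADL (Barthel Index and NEADL scored by close relative or nursing home staff". It introduces the list by purpose: "The following variables will be registered for descriptive purposes and in order to assess balance between the groups with respect to prognosis".

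The only covariate rule stands under Data analyses and statistical power: "The material will be checked for any inequality in the distribution of important prognostic variables between the two arms, and if such are present", then "they will be adjusted for by including these in appropriate regression models". That section gives the primary endpoint a stratified linear regression, and binary outcomes chi-square tests and logistic regression. It names no model for continuous secondary scores such as Barthel and NEADL. Nowhere is the pre-fracture score made a planned covariate, and no change score is defined.

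**The concern.** The trial enrols people from independent home-dwellers to permanent nursing-home residents, and its Discussion accepts that this makes the sample more heterogeneous. Part of the variation in ADL at follow-up will be variation that existed before the fracture. A model containing the pre-fracture score removes that part from the error term; a model without it does not.

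The stated rule makes adjustment depend on seeing an imbalance. The precision gained from a baseline covariate comes from how well it predicts the outcome, not from whether the arms happen to differ on it. The rule therefore omits the covariate in most trials in which it would help. It also leaves the choice of model until the baseline data have been inspected, and gives no threshold for inequality.

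At stake is the width of the confidence intervals for a named secondary objective. Recruitment closed at 332 against an aim of 370, and the Discussion itself raises the risk of a type 2 error. The sample can no longer grow, but the analysis can still be made more efficient.

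**Working it through.** **The plan's own figure.** The article judges 300 patients sufficient, expects 20% to die before 4 months, and aims to randomise 370. Check: 300 / (1 - 0.20) = 375, close to 370. The 300 itself cannot be rebuilt, because no effect size, SD, power or alpha is given.

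**Inputs from the article.**
- Randomised: 332 (Time plan of the study).
- Expected deaths by 4 months: 20% (Data analyses and statistical power), so 332 x 0.80 = 265.6, about 266 evaluable.
- One-year mortality: 23% in the hospital's retrospective series (Background), used only to approximate 12 months: 332 x 0.77 = 255.6, about 256.

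**Assumptions, not in the article.** Two-sided alpha 0.05, 80% power, equal arms, no loss other than death, and a correlation r between pre-fracture and follow-up score of 0.3 to 0.7 beyond the nursing-home stratum. The SD is the one that remains without the baseline score in the model.

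**Formulas.**
- Standard error ratio, adjusted to unadjusted: sqrt(1 - r^2).
- Detectable difference, unadjusted: (1.96 + 0.84) x 2 / sqrt(N). Adjusted: the same times sqrt(1 - r^2).
- Equivalent unadjusted sample size: N / (1 - r^2).

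**Results at 4 months.** Unadjusted: 2.80 x 2 / sqrt(265.6) = 0.344 SD.

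| r | SE ratio | SE reduction | Detectable difference (SD) | Equivalent N | Power for an effect of 0.344 SD |
|---|---|---|---|---|---|
| 0 | 1.000 | 0% | 0.344 | 266 | 80% |
| 0.3 | 0.954 | 5% | 0.328 | 292 | 84% |
| 0.5 | 0.866 | 13% | 0.298 | 354 | 90% |
| 0.7 | 0.714 | 29% | 0.246 | 521 | 97.5% |

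**Results at 12 months.** The detectable difference falls from 0.350 SD to 0.334 (r = 0.3), 0.303 (r = 0.5) or 0.250 SD (r = 0.7).

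**Does adjusting on observed imbalance recover the loss?** A simulation with 133 patients per arm and 8,000 runs per setting took unequal to mean a baseline difference at about p < 0.05. That threshold is an assumption, and under randomisation it triggers adjustment in about 5% of trials.

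| r | Power, never adjusting | Power, adjusting if unequal | Power, always adjusting | Type I error, adjusting if unequal |
|---|---|---|---|---|
| 0.3 | 79.5% | 79.8% | 83.2% | 4.7% |
| 0.5 | 80.0% | 81.1% | 89.9% | 4.3% |
| 0.7 | 79.4% | 81.2% | 97.4% | 3.4% |

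Power is at an effect of 0.344 SD. The conditional rule recovers little of the lost power, and its type I error lies below 5%. A looser reading of unequal would trigger adjustment more often.

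**The case against.** **The article does not forbid baseline adjustment.** It does not say that the pre-fracture scores serve description and balance alone, and it names no model for continuous secondary scores. A fuller protocol or analysis plan could add one. This stands as a limit: a reader might infer that adjustment is ruled out, and the text does not go that far. But the article does more than stay silent. It gives these scores a purpose and states a trigger for adjustment, and that trigger is what needs changing.

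**The size is assumed.** This also stands. The article gives no correlation. It notes a marked ceiling effect for Barthel, and the informant may change between assessments as patients move into institutions; both may lower r. At r = 0.3 the gain is small. A reader might infer that pre-fracture function explains most of the follow-up spread, or that every patient has a baseline score. Neither is supported: the Data collection section describes pursuing missing proxy data.

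**The baseline is not a clean one.** Relatives or staff report it during the stay, after randomisation, and in-hospital variables are not acquired blind. The geriatric ward contacts relatives about pre-fracture status, while the orthopaedic ward has no routine geriatric assessment. If reporting differed by ward, adjustment would move the estimate by the regression slope times that difference. This is the strongest objection. It does not defeat the change, but it is why the unadjusted estimate must be shown as well.

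**ADL is secondary.** The Discussion treats significant secondary effects as exploratory if the main outcome is negative. This limits the weight of the point.

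**Conclusion.** The concern holds as a loss of precision on a secondary objective. Following the stated rule, the ADL comparisons would usually omit the scale's own pre-fracture score. With about 266 evaluable patients and r from 0.3 to 0.7, planned adjustment lowers the standard error by 5% to 29% and the detectable difference from 0.34 SD to between 0.33 and 0.25 SD. The gain is slight at the low end and material from about r = 0.5. The range rests on an assumed correlation beyond the nursing-home stratum and on no loss other than death.

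A reader might infer that the plan produces biased ADL results or false positives because the data choose the model. That does not follow. Randomisation keeps the unadjusted comparison unbiased, the trigger depends on baseline rather than outcome data, and in the simulation the rule made the test conservative. The point should be acted on, but it does not threaten the validity of the trial.

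**What to change.** Before the effect analyses start (the article expects summer or autumn 2012), specify the following:

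1. Barthel and NEADL at 4 and at 12 months are each analysed by linear regression on arm, nursing-home stratum and the same scale's pre-fracture score, whatever balance is observed.
2. Patients with a missing pre-fracture score stay in the analysis by a simple stated method, for example single imputation of the baseline made without regard to arm.
3. For these endpoints, adjustment for observed imbalance is used in supportive analyses only.
4. The estimate without the pre-fracture score is reported alongside.

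The cost is a few sentences and no new data collection, since both scales are already in Table 1. The small downside is that the covariate is a proxy report obtained after randomisation by unblinded staff; item 4 lets readers see whether the result depends on it.

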### Consent and enrolment

Patients are randomised in the Emergency Department in accordance with procedures already established for a recently finished trial [60]. The orthopaedic resident on call assesses all patients admitted for a suspected hip fracture, decide upon the choice of operative treatment, obtain informed consent/assent, and perform the randomisation.

Cognitively intact patients are included on the basis of written, informed consent. We have developed a full information leaflet for cognitively intact patients and a simplified and shortened version. If the latter version is used, a close relative should receive the full version of the patient information. Those who are totally unable to give a valid informed consent will be included on the basis on presumed consent in combination of assent from the nearest relative. The relative is asked for assent at the earliest possible occasion. If a patient that has been assessed as unable to give an informed consent becomes lucid again, he or she is asked to give an own informed consent. If the relative of a patient included on the basis of presumed consent (or the patient him/herself after having become lucid) resists inclusion, all data from that patient will be destroyed.

A large proportion of hip fracture patients are either demented or delirious (or both) on admission. These groups are presumed to be more vulnerable to the quality of hospital care than those that are cognitively intact, and thus important to include in studies of this kind. We have in a previous randomised trial of femoral neck fractures [60] included patients without the ability to give an informed consent, following guidelines from the ethical committee. In that study, 23% of the patients (10% of those admitted from their own homes) were judged by the recruiting surgeon in the Emergency ward to be unable to give an informed consent, either due to dementia or delirium. We have been careful to establish routines for inclusion that take care of these people's dignity and rights, and stay in a close dialogue with respect to this with the Regional Committee for Ethics in Medical and Health Research and the Data Protection Officer.

### Data collection

Background information, information regarding surgical and anaesthetic procedures, drug use, and proxy information on pre fracture ADL function and cognitive function is collected during the acute stay, by the study physician and a study nurse. On day 1 a research nurse attaches an ActivPal® sensor on the anterior aspect of the non-affected thigh. The sensor is worn for a minimum of 72 hours or until discharge or until it has to be removed through patient action or choice.

Research assistants continually scrutinise study forms for missing data. Missing data from proxies are collected through telephone calls. Electronic hospital records give further information on clinical examinations, medication, blood tests and other investigations performed during the index stay.

The 4-month registration is performed by a research assistant at the site where the patient is living, irrespective of location. This might be the patient's own home, a nursing facility or a rehabilitation institution. The time window is 4 months ± 3 weeks. 

The 12-month registration is performed similar to the 4-month registration. The time window is 12 months ± 3 weeks. For details on data collection and questionnaires, see Table 1.

**Table 1 T1:** Variables and time-points for assessment

**Pre-fracture characteristics registered during index stay**	**Index stay**	**4-months follow-up**	**12-months follow-up**
IQCODE	Demographics	CERAD 10 words memory task	CERAD 10 words memory task
CDR	Type of fracture	MMSE	MMSE
Barthel	Surgical and anaesthetic procedures	Cock drawing test	Cock drawing test
NEADL	Medication	CDR	CDR
Cornell	CCI	Barthel	Barthel
	ASA score	NEADL	NEADL
	APACHE score	Cornell	Cornell
	SAPS II	SPPB	SPPB
	ECG	Weight	Weight
	Medication	Hand-dynamometry Micronutrients in blood (as during index stay)	Hand-dynamometry Micronutrients in blood (as during index stay)
	Hand-dynamometry	Markers of bone turnover (as during index stay)	Markers of bone turnover (as during index stay)
	Weight, height		
	CAM daily		
	MDAS		
	ActivePAL (from September 2011)		
	Micronutrients in blood (Vit A, Thiamine, Pyridoxine, Folate, Vit B_12_, Vit C, 25-Hydroxy-Vit D, Vit E, Vit K_1_, Homocystein, Zink)		
	Markers of bone turnover (Osteocalcin, Undercarboxylated osteocalcin, Parathyroid hormone, Bone-specific alkaline phosphatase, Insulin-like growth factor 1, Carboxy-terminal collagen crosslinks (CTX), Aminoterminal propeptide of type I collagen (PINP))		

Abbreviations: ALP = Alkaline Phosphatase. APACHE = Acute Physiology And Chronic Health Evaluation. ASA = American Society of Anaesthesiologists. CAM = Confusion Assessment Method. CCI = Charlson Co-morbidity Index. CDR = Clinical Dementia Rating. ECG = electrocardiogram. IGF = Insuline-like Growth Factor. IQCODE = Informant Questionnaire on Cognitive Decline in the Elderly. MDAS = Memorial Delirium Assessment Scale. NEADL = Notingham Extended Activities of Daily Living Scale. SAPS = Simplified Acute Physiology Score. SPPB = Short Physical Performance Battery. Vit = Vitamin.

### Data analyses and statistical power

The primary analyses will be done in a modified intention-to-treat analysis including the sample of patients completing the CERAD 10 words test and CDR at 4 months. The weighting of the components of the primary endpoint (see primary endpoint section above) will be definitely decided upon before any analyses of the treatment effect are initiated. A separate per protocol analysis will be undertaken. The primary endpoint will be analysed by stratified linear regression. If the assumption of normality turns out to be violated, additional analyses will be performed on transformed data as well as by non-parametric methods (Mann–Whitney test). Binary outcomes will be analysed by chi square tests and logistic regression models. The material will be checked for any inequality in the distribution of important prognostic variables between the two arms, and if such are present, they will be adjusted for by including these in appropriate regression models.

Sensitivity analyses will be performed by imputing missing values in different conservative ways, e.g. by imputing the worst observed score of the treatment group and also by random sampling from the observed scores in the treatment group.

The main analyses of 12 months data will be carried out including patients with responses registered at that time point. Additional sensitivity analyses will be performed in the sample of all randomised patients using different methods of imputation as described above as well as by carrying the four month observation forward.

If an interaction test is statistically significant at the 0.10 level, we will analyse the effect upon the endpoints separately in the following subgroups: patients admitted from nursing homes or not, and patients with and without pre-fracture dementia.

We also register the time window from admittance to start of surgery, as any group difference here may also impact severely on the outcome [7].

No data are available allowing us to carry out precise power estimates based on our primary endpoint. Based upon previous experiences with CDR, however [61] ([name], unpublished data), we judge 300 patients to be sufficient to detect clinically meaningful differences. As 20% of hip fracture patients can be expected to die before the 4 months follow up [6], we aim for 370 patients to be randomised.

The results of the trial will be published in accordance with the CONSORT guidelines [62]. Publishing the protocol of the Oslo Orthogeriatric Trial is in accordance with the recommendation to publish RCT protocols for complex interventions [63].

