### Primary endpoint

We will construct a composite endpoint using two instruments:

· Clinical Dementia Rating Scale (CDR) [42], is a scale measuring severity of dementia. The scale consists of six questions, each rated 0–3, adding up to a sumscore of 0–18 ("sum of boxes"), or a categorical score between zero and 3. We plan to use the "sum of boxes" scoring. The correlation between the two scoring systems is high, approximately 0.9 [43,44]. The scale is frequently used in dementia treatment trials, and has been shown to be valid and reliable [45]. CDR is scored based on the best available sources, as a combination of patient and proxy information (relative, staff in nursing home or home nursing service).

· The 10 words memory task from the Consortium to Establish a Registry for Alzheimer's Disease battery (CERAD) [46]. This test is shown to be sensitive for memory changes in persons that have a good or fairly good cognitive functioning. We will use the immediate recall and the delayed recall parts of this task, i.e. two scales.

We will normalise these three scales into a 0–100 scoring (and reverse the CDR scoring as this is scaled in the opposite direction) to compute the composite endpoint. Before the randomisation allocation variable is added into the database, we will examine the proportion of patients in the lower *vs* the higher spectrum of performance as well as the correlation between each pair of scales. This information will be used to choose an appropriate weight to each of the scales before combining them. The distribution of the composite endpoint will also be examined.

The primary endpoint is assessed after four and twelve months, by a trained research assistant blinded to allocation.

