Since the focus of the trial is cognition and prevention of cognitive decline, we have defined wider eligibility criteria than many other hip fracture trials. Nursing home residents and other patients with pronounced frailty are particularly vulnerable to sub-optimal clinical quality, and are at high risk of developing dementia and of worsening of a pre-existing dementia. Accordingly, these patients are included in our study, even though they have a very limited rehabilitation potential with respect to for instance return to own home or independent mobility. Likewise, we have not set a lower age limit for our study, but exclude those who fracture their hip due to a high energy trauma. Nearly every hip fracture patient is above 70 years, but, in our opinion, a hip fracture due to a low energy trauma in a person below 70 is an indicator of frailty, making inclusion in this trial logical. The same reasoning applies to those with pathological fractures, for instance due to malignancy. These patients are also prone to delirium, and thus should be eligible for our study regardless of their potential to achieve independent gait function, unless their life expectancy is very short. Our wide inclusion criteria imply a good external validity, but at the expense of an increased heterogeneity in the patient sample.

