It follows from the inclusion criteria that our participants will have very different levels of cognitive performance, from those with severe dementia to those who function well. Our hypothesis is that optimal and integrated care may help to preserve cognitive function on the entire range of pre-fracture functioning. This assumption makes the choice of primary endpoint challenging. We decided to use a composite endpoint consisting of immediate and delayed recall from the 10 word memory list and the CDR, as we believe that the first instrument will be able to capture differences between cognitively well functioning participants, and the latter one differences in the lower part of the functional spectrum. Composite endpoints in randomised trials are sometimes regarded as controversial [64,65]. The critique is, however, mostly related to the situation where the elements of the composite are of different importance, and in particular when any group difference is most likely to be driven by the less important part. The same kind of reasoning is appropriate for dementia research, where an individual quantification of impairment, disability and handicap is recommended [66]. However, in our study the composite endpoint does not reflect different domains, but aims at measuring the same construct, i.e. cognitive functioning. We consider the elements to be equally important, but we consider one single scale to have insufficient sensitivity to catch every relevant change. Moreover we anticipate the variability within each scale to be too high, so that it will be impossible to catch clinically meaningful differences with reasonable power by the use of one single scale. The normalising of each scale to a 0–100 scaling is in accordance with established practice within quality of life research [67], and the use of CDR as a global measure of cognitive functioning is in accordance with official recommendations [66]. We will certainly report the results also for each element of the composite, as generally recommended for studies utilising composite endpoints [64,65].

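### Requiring a completed 10-word test for the primary analysis drops survivors too impaired to be tested, even when a CDR score exists, and so selects on the outcome if the intervention affects cognition.

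*Protocol article*

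**What the plan says.** Data analyses and statistical power fixes the primary set as a "modified intention-to-treat analysis including the sample of patients completing the CERAD 10 words test and CDR at 4 months". Both instruments are required. The article does not say that a survivor who cannot be tested is scored at the floor or analysed on CDR alone.

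The two instruments have different jobs:

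- On the word test, Primary endpoint says: "This test is shown to be sensitive for memory changes in persons that have a good or fairly good cognitive functioning".
- The Discussion gives CDR the other end of the range, namely "the latter one differences in the lower part of the functional spectrum".
- The two also differ in how they are obtained: "CDR is scored based on the best available sources, as a combination of patient and proxy information" (Primary endpoint). The word test needs the patient to perform.

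The trial enrols patients "from those with severe dementia to those who function well" and states its aim broadly: "Our hypothesis is that optimal and integrated care may help to preserve cognitive function on the entire range of pre-fracture functioning" (both Discussion).

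For missing values, the analysis section plans sensitivity analyses. These impute either the worst score observed in the treatment group or a random draw from that group's observed scores. Secondary endpoints lists CDR and the word test as separate outcomes.

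**The concern.** Being testable at 4 months is a post-randomisation event that depends on the cognition being measured. If the intervention preserves cognition, more control than intervention patients become untestable and leave the primary comparison. The remaining controls then look better than the control arm as a whole, and the estimated benefit shrinks.

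The rule also works against the reason for the composite. An untestable survivor is the kind of patient for whom a proxy-informed CDR was included, yet that score does not count in the primary result. At stake is the ability to detect a real effect, in a trial whose Discussion already names type 2 error as a possible weakness.

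**Working it through.** **The plan's own figure.** Data analyses and statistical power judges 300 evaluable patients sufficient, expects 20% deaths before 4 months and aims for 370. Check: 300 / (1 - 0.20) = 375, and 370 × 0.80 = 296, so 370 reproduces to within rounding. The 300 itself cannot be reproduced, because no alpha, power, effect size or SD is given. The allowance covers deaths only.

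**How many patients the rule could remove.** Time plan of the study reports 332 randomised. Expected survivors: 332 × 0.80 = 265.6. Let u be the share of survivors who cannot be tested (assumed; the article gives none).

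- u = 10%: 265.6 × 0.10 = 26.6 leave, 239 remain.
- u = 20%: 265.6 × 0.20 = 53.1 leave, 212 remain.

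**What the rule does to the estimate.** This is an illustrative simulation. Survivors per arm: 265.6 / 2, about 133. The assumed true shift is 0.3236 SD, which is about what 150 per arm could detect with 80% power at two-sided 5%: (1.960 + 0.842) × √(2/150) = 0.323. Patients below a fixed cognition threshold are removed from both arms. The threshold is set so that 10, 15 or 20% of controls fall below it. With the shift, the intervention arm then loses Φ(-1.282 - 0.324) = 5.4%, Φ(-1.036 - 0.324) = 8.7% or Φ(-0.842 - 0.324) = 12.2%. The 10-20% here is thus a control-arm share, not the share of all survivors used above.

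| Controls untestable | Completer difference (original SD units) | Standardised difference among completers | Power |
|---|---|---|---|
| 0% | 0.324 | 0.324 | about 0.74 |
| 10% | 0.244 | 0.286 | 0.59 |
| 15% | 0.221 | 0.267 | 0.53 |
| 20% | 0.204 | 0.259 | 0.48 |

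Fall in the standardised difference: (0.324 - 0.286) / 0.324 = 12% up to (0.324 - 0.259) / 0.324 = 20%.

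**Weaker selection.** When testability correlates only 0.8 with cognition, power is 0.64, 0.59 and 0.54. At correlation 0.5 it is 0.68, 0.66 and 0.61. Part of every drop is plain loss of numbers: random loss of 10, 15 or 20% from both arms gives 0.70, 0.69 and 0.65.

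**Second model.** Here an equally weighted 0-100 composite is driven by latent cognition, with a uniform benefit of 0.3 SD. The true difference of about 6.1 points becomes 4.8, 4.0 and 3.5 among completers when 10, 20 and 30% of controls are untestable. With no treatment effect the completer difference stays within 0.04 points of zero.

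**The planned imputations.** Under the hard-truncation model, worst-observed-score imputation within arm gives power of about 0.72-0.74, close to no loss. A random draw from an arm's observed scores leaves that arm's expected mean equal to its completer mean, so on average it reproduces the completer difference.

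**The case against.** The case against is substantial.

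- **The plan already has an analysis that addresses this.** Worst-observed-score imputation recovers nearly all the lost power in the model above. This stands. But it is a sensitivity analysis, named only as an example, and it does not use the patient's own CDR.
- **A reader might infer that all severely impaired survivors are dropped.** The text does not support that. A patient who attempts the list and recalls nothing scores 0 and has completed the test, and CDR can then separate such patients. The point concerns only those who cannot be tested. A fuller protocol or analysis plan, not shown here, may say how they are scored; the article fixes the set without doing so.
- **A reader might infer that the observed CDR is thrown away.** It is lost only from the composite. CDR is a secondary endpoint in its own right, and the Discussion promises results for each element.
- **A reader might quote the attenuation in original units:** (0.324 - 0.244) / 0.324 = 25% up to (0.324 - 0.204) / 0.324 = 37%. That overstates the effect on the test, because truncation also shrinks the SD.
- **A reader might take the 23% unable to consent (Consent and enrolment) as the untestable share.** That figure is from another trial, was judged on admission and includes delirium. It shows only that severe impairment is common.
- **A reader might fault the exclusion of deaths.** That is not part of this point. The plan calls its set modified, sizes it for survivors and reports mortality separately, and the set proposed below also requires being alive at 4 months.

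**Conclusion.** The point holds for survivors who are untestable because of poor cognition. The primary set conditions on a post-randomisation event tied to the outcome, and it leaves CDR scores out of the composite for patients in the range CDR was meant to cover. If the intervention affects cognition, the primary estimate is pulled toward zero. Under a strict null there is no bias, so a reader should not infer that this mechanism produces false positives.

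The size is uncertain because the untestable share and the effect size are both assumed. At 10-20% of survivors, about 27-53 of roughly 266 leave. In the hard-truncation model the standardised difference falls by about 12-20% and power falls from about 0.74 to 0.59-0.48, less if testability tracks cognition loosely. The mechanism does not depend on these figures. What remains in dispute is which analysis carries the primary conclusion, and the completer analysis is the weaker choice.

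**What to change.** Make the change before the allocation variable is added to the database, the same point by which Primary endpoint requires the weights to be chosen:

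1. Define the primary set as all randomised patients alive at 4 months with a CDR.
2. Score immediate and delayed recall at the floor when the test could not be done for cognitive reasons.
3. Impute recall missing for other reasons from CDR, MMSE, the nursing-home stratum and IQCODE, all of which the trial collects.
4. Report non-completion of the word test by arm and reason.
5. Keep the completer analysis as a sensitivity analysis.

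The article does not say whether the reason for non-completion was recorded. If it was not, classify it from CDR and MMSE, blind to allocation.

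Cost: a change of wording in the analysis plan and some blinded classification work. The floor rule will produce a cluster of low values. The transformed and non-parametric analyses already planned for non-normality can be used to check its influence.
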